**4.8 Outcomes:**

***Primary:*** The primary outcome measured will be exclusive breastfeeding at 3 months, or 3 months corrected if the infant was born prematurely. Exclusive breastfeeding is defined as no other milk intake than maternal milk. Health benefits have been demonstrated after as little as two weeks of exclusive breastfeeding50. However, a larger number of studies have reported positive health outcomes after two to four months of exclusive breastfeeding27, 50-52. Exclusive breastfeeding was chosen as primary outcome as it is a quantifiable measure. Partial breastfeeding is more difficult to define as it may range from very little breastfeeding to almost exclusive breastfeeding, which would have an impact on the magnitude of benefits imparted by breastfeeding. Breastfed babies will be defined as babies who receive no other milk than breast milk, whether directly from the breast or as expressed breast milk.

***Secondary:*** All measurements will be collected at corrected age if infant was born prematurely. 1) Exclusive breastfeeding at six months; 2) Partial breastfeeding at three months; 3) Partial breastfeeding at six months; 4) Number of re-hospitalization for jaundice in the first six months of life; 5) Number of re-hospitalization for non-jaundice related causes in the first six months of life; 6) Number of physician encounters in first 6 months of life; 7) Number of mothers seeking breastfeeding help; 8) Amount and type of breastfeeding support given by child’s primary physician in first six months of life

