# 5. ANALYSIS

**5.1 Sample size:**

In our previous study of infants hospitalized for jaundice, the rate of exclusive breastfeeding at 3 months was roughly 50%17. However, we expect that rate to be lower given the reasons stated above (high level of education in the study population). Moreover, higher levels of education have been shown to be associated with higher rates of participation in different types of study53-55, making the selection bias hypothesis even more likely. Nevertheless, to be conservative we picked 50% as the rate of exclusive breastfeeding at 3 months.

Based on a systematic review of interventions to promote breastfeeding, a 25% increase in the rate of breastfeeding at 3 months is plausible18. In that meta-analysis of randomized controlled trials combining educational and support programs, breastfeeding rates in the short term increased by 36% (95% CI 22-49%), putting our 25% increase estimate at the low end of the confidence interval. This would result in an additional one in four women breastfeeding. An informal survey of hospital based consultant pediatricians confirms this as a clinically significant increase. Setting the probability of type I error at 0.05, a sample size of 58 mothers per group would result in a power of 80% to detect such an increase.

The anticipated number of patients lost to follow-up for the primary outcome is low given that our population of interest consists of young infants. Previous studies in such young children conducted at CHEO have high follow-up rates when primary outcomes were determined through phone follow-up56,57. As a result, we expect a loss to follow-up of no more than 7.5%. To account for this, we would therefore need to recruit 62 patients in each group (Appendix 9).

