**5.2 Quantitative Data Analysis**

Baseline characteristics of the study participants will be summarized using descriptive statistics. Continuous variables will be summarized using the mean, median, standard deviation, interquartile range, and range. Discrete variables will be summarized using frequencies and percentages.

The primary analysis will be a comparison between groups of breastfeeding rates at 3 months using Fisher's exact test. All tests will be two-sided, with p-values less than 0.05 taken to be statistically significant. Time to discontinuation of breastfeeding will also be compared between groups graphically using Kaplan-Meier curves, and statistically using the logrank test. Mothers still breastfeeding at the time of data collection will be treated as censored observations. The rates of breastfeeding failure (defined as discontinuation of breastfeeding before the infant is 6 months old) will be compared between mothers of infants admitted to the hospital with jaundice and randomized to the control group, and those in the community as per the breastfeeding rates determined by the Infant Care Survey37 using Pearson’s chi-squared test. Poisson regression models will be used to compare the number of re-hospitalizations for jaundice, hospitalizations for non-jaundice related causes, as well as physician encounters (emergency room visits, community pediatricians / family physicians) in both groups of patients throughout their first 6 months of life. Fisher’s exact test will be used to compare the proportion of mothers in each group seeking breastfeeding help once discharged from the hospital.

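### The Poisson analysis of physician encounters and hospitalizations has no allowance for overdispersion; if visit counts vary more than Poisson, its p-values and intervals are too optimistic

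*Protocol*

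**What the plan says.** Section 5.2 of the protocol fixes the model family for three secondary count outcomes: "Poisson regression models will be used to compare the number of re-hospitalizations for jaundice, hospitalizations for non-jaundice related causes, as well as physician encounters". The last of these combines emergency department visits with visits to community pediatricians and family physicians. The comparison is made "in both groups of patients throughout their first 6 months of life", and the general rule of the section applies: "All tests will be two-sided, with p-values less than 0.05 taken to be statistically significant".

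Section 4.8 lists the outcomes, among them "Number of physician encounters in first 6 months of life", and adds: "All measurements will be collected at corrected age if infant was born prematurely".

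The protocol does not mention a robust or scaled variance, an overdispersion check, a negative binomial alternative or an offset for time observed. It does not rule any of them out. It gives no expected mean or variance for any of the counts.

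**The concern.** A Poisson model fitted in its standard form takes the variance of each count to equal its mean. Physician encounters may well not behave that way. Illness-driven visits tend to recur in the same infant, and section 4.7 shows that the infants will differ in gestational age, septic work-up and antibiotic treatment. If the variance exceeds the mean, the model-based standard errors are too small, p-values fall below 0.05 too often and confidence intervals are too narrow.

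Time at risk also differs between infants. They enter at any age below 1 month (section 4.3), some will be lost before 6 months, and preterm infants are assessed at corrected age (section 4.8).

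Health care utilization is a stated secondary objective (section 1.2). Section 8 intends to judge the effect of the program on child health from physician encounters and hospitalizations. A spuriously significant difference would feed directly into that conclusion.

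**Working it through.** **The plan's own figure.** No figure is stated for the count analyses. The only sample size is for the primary outcome: a control rate of 50% ("to be conservative we picked 50% as the rate of exclusive breastfeeding at 3 months"), a gain of 25 points to 75% ("This would result in an additional one in four women breastfeeding"), two-sided 0.05 and 80% power. With a pooled variance and no continuity correction:

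n = [1.96·√(2·0.625·0.375) + 0.842·√(0.5·0.5 + 0.75·0.25)]² / 0.25² ≈ 57.7, so 58 per group.

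This agrees with section 5.1 and does not depend on the point made here. Section 5.1 raises the number to 62 per group for loss to follow-up.

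**Inputs for the count analyses.**
- From the protocol: two-sided 0.05, 58 or 62 per group, equal allocation, and loss of at most 7.5% (stated for the primary outcome).
- Assumed, because the protocol gives none: a mean count from 0.1 (rare readmissions) to 8 (visits), with 6 as the main value for visits, and a variance/mean ratio φ from 1 to 3.

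**How much heterogeneity is needed.** If infants differ in their underlying visit rate with coefficient of variation CV, then φ = 1 + mean × CV². At a mean of 6, a CV of 29% gives 1 + 6 × 0.29² ≈ 1.5, and a CV of 41% gives 1 + 6 × 0.41² ≈ 2.

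**Size of the model-based test.** The log rate ratio has model-based variance 1/S₁ + 1/S₀, where S₁ and S₀ are the total counts in the two groups. Its true variance is φ times that, so the Wald statistic has standard deviation √φ under no effect:

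true size = 2·[1 − Φ(1.96/√φ)], and coverage = 1 − true size.

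The simulation used 20,000 trials per scenario, gamma-Poisson counts with no true effect, 62 per group and mean 6.

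| φ | 1.96/√φ | Size, formula | 95% CI coverage | Size, simulated, model-based | Size, simulated, robust |
| --- | --- | --- | --- | --- | --- |
| 1 | 1.96 | 0.050 | 95% | 0.053 | 0.054 |
| 1.5 | 1.60 | 0.110 | 89% | 0.109 | 0.051 |
| 2 | 1.39 | 0.166 | 83% | 0.166 | 0.051 |
| 3 | 1.13 | 0.258 | 74% | 0.260 | 0.054 |

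Results with 58 per group are nearly the same.

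**Rare readmissions.** At mean 0.1 with 62 per group, the model-based test has size 0.028 at φ = 1, 0.065 at φ = 1.5 and 0.103 at φ = 2. If every infant had 0 or 1 readmission, φ would be 1 − 0.1 = 0.9, which is below 1. The test is therefore conservative here unless a few infants are readmitted repeatedly.

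**Time observed.** At mean 6, φ = 1 and 62 per group, with each lost infant leaving at a random point in the window:
- 7.5% loss in both groups: size 0.065 without an offset, 0.051 with one.
- 2% against 13% loss (assumed): size 0.139 without an offset, 0.051 with one. A robust variance without the offset still gives 0.112.

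The robust variance and the offset therefore deal with different problems.

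**The case against.** The strongest reply is that section 5.2 names a model family and nothing more. A robust variance and an offset are both options within Poisson regression, and such detail is commonly left to a statistical analysis plan, which is not at hand. That is fair: their absence is not in itself an error, and the protocol's sentence does not forbid the remedy. What remains is that the sentence, carried out as written, leads by default to model-based errors for a pooled visit count, and a safer choice costs almost nothing.

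Second, no document gives a variance. Scheduled routine visits made by most infants would lower φ, perhaps below 1; at φ = 0.7, 1.96/√0.7 = 2.34 and the size is about 0.02, which is conservative. This also stands, and it makes the finding conditional.

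Three stronger readings are tempting, and the documents do not support them.
- A reader might infer that Poisson regression assumes equal follow-up. It does not, since an offset is a standard part of it and is unmentioned rather than excluded. With the stated 7.5% loss balanced between groups, leaving it out moves the size only to about 0.065. The larger figure needs an imbalance in loss that nothing in the protocol suggests, and randomization should balance preterm birth and age at entry on average.
- A reader might infer that readmission results will be anti-conservative too. For rare counts without overdispersion the test errs the other way.
- A reader might infer that a false positive is likely. A true size of 11% to 26% is well above 5% but is not that.

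**Conclusion.** The point holds in conditional form, as a small improvement to a secondary analysis. If physician encounters are overdispersed and model-based errors are used, the nominal 5% test has a true size of about 11%, 17% or 26% at φ of 1.5, 2 or 3. The values of φ and the means are assumptions. With no overdispersion the planned test has about its nominal size, and the robust version is no worse (0.054 against 0.053). The case is weakest for readmissions. The Fisher test on the primary outcome and the 58 per group are untouched.

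**What to change.** In section 5.2, specify Poisson regression with a robust (sandwich) variance, or negative binomial regression, for the three count outcomes, with the log of time observed as an offset. State when the counting window opens and closes for each infant, including preterm infants assessed at corrected age, so that the offset is well defined.

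This needs no extra patients. The diary already asks for the date of each medical assessment, and the scheduled calls supply a date of last contact. The downside is wider intervals when counts are overdispersed, by a factor of about √φ: 1.22, 1.41 and 1.73 at φ of 1.5, 2 and 3. One limit should be noted: for sparse and strongly overdispersed counts the robust test stays slightly liberal (0.077 at mean 0.3 and φ = 3 with 62 per group, against 0.244 for the model-based test).

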**5.3 Qualitative Data Analysis**

All semi-structured interviews will be audio taped and transcribed verbatim. The transcription of the audiotapes will allow for accurate reporting of the responses and for interpretation of responses within the context of the entire discussion. Each participating mother will be provided with the opportunity to verify the transcript of her interview. This verification will ensure the quality and accuracy of the data. All qualitative data analyses will be conducted using Nvivo 8 software. Inductive analysis will be used to identify categories, patterns and themes that are embedded in the data and seem meaningful to the interviewees58.

**5.4 Feasibility**

In 2006, there were 116 breastfeeding infants admitted with jaundice to the Children’s Hospital of Eastern Ontario who met the eligibility criteria of this study, as determined by the CHEO Health Record Analyst. Given that the average length of stay for these patients was 2.5 days, we estimate that 90% of the families admitted to the hospital will be approached, and that 80% of those will consent to participate in the study, for a total enrolment rate of 72%. Based on these numbers, the period of recruitment will last 18 months to achieve our total sample of 124, for a total study duration of 2 years.

Our 90% approaching rates are based on strong strategies put in place to avoid missing eligible patients. As mentioned above, the average length of stay is 2.5 days for babies admitted with jaundice, with very few babies staying less than 24 hours. The admission log will be checked every morning from Monday to Friday by the research assistant, and eligible families will be approached. On Friday afternoon, the research assistant will leave 2 to 3 opaque envelopes in a secure location on the wards. On Saturday and Sunday mornings, the attending physicians responsible for the inpatient units will determine if any of the babies admitted over the previous 24 hours are eligible for the study Eligible families will then be approached by the attending physician on that day. If the family agrees to participate, the attending physician will open the opaque envelope, and communicate with the lactation consultant if randomized to the intervention group. The family will then meet with the lactation consultant if randomized to the intervention group, since the lactation consultant will be available 7 days a week. The attending physician will then be instructed to leave a voice mail message with the research assistant, so that follow-up can be ensured. On Monday morning, the research assistant will pick up the unopened envelopes from the secure location. One of the investigators (CP, AP) will be available by pager to answer the attending physician’s questions, if any. If we find that less than 90% of families are being approached, other strategies will be put in place, such as 24 hours paging of the investigators and/or research assistant by the admitting clerk.

Previous studies done at CHEO with more aggressive interventions were shown to have consent rates of 60%59. These studies looked at drug intervention therapies in patients presenting to the emergency department, a highly stressed population. Given that our intervention (breastfeeding support offered by a lactation consultant) presents no risk at all, and our population is highly motivated, a consent rate of 80% seems highly reasonable. Also, in the PI’s retrospective study examining length of breastfeeding in jaundiced patients, over 60% of mothers who were mailed a questionnaire participated in the study, showing that this population is highly motivated17. Given that our intervention (breastfeeding support offered by a lactation consultant) presents no risk at all, and our population is highly motivated, a consent rate of 80% seems highly reasonable.

# 6. TRIAL MANAGEMENT

# 6.1 Day to day management

The principal investigator (CP) and study coordinator will be responsible for the overall supervision of the study. A first study site research assistant will be responsible for recruiting patients, allocating patients to their intervention, communicating with the lactation consultant when patients are randomized to the intervention group, and conducting the semi-structure interviews. A second research assistant, blinded to group allocation, will collect and enter the data, and provide phone follow-ups one week after discharge, and at 2, 3, 4, and 6 months. An International Board-Certified Lactation Consultant (IBLC) will provide the breastfeeding support intervention.

Data entry and management will be provided by Clinical Research Group of the Children’s Hospital of Eastern Ontario Research Institute. The statistician (NB) will be responsible for statistical data analysis and will assist in manuscript preparation. ACP and RC will provide support to the PI and study coordinator in implanting the study. KF and KM will provide guidance in the qualitative component of the study.

Breastfeeding support equipment (breast pumps, collection kits, nipple shields, freezer bags, nursing pads) will be provided at lower cost by Medela Canada Inc. A letter detailing cost of supplies is attached (Appendix 10). The company’s sole involvement with the study is the provision of breastfeeding equipment. They will not be involved in the analysis, interpretation, or writing of the final manuscript.

# 7. ETHICAL CONSIDERATIONS

Patients will only be entered into the study after free and informed consent (Appendix 2) has been received from the mother. In addition, they will be free to withdraw at any point in time and will receive the same standard of medical care given to all jaundiced patients admitted to the pediatric ward at CHEO. The data collected during this trial will be held confidential.

The intervention in this trial will be unlikely to have any adverse effect on the patient or patient’s mother, as there is no risk associated with filling out a questionnaire, a booklet, and meeting with a lactation consultant. There will be no discomfort to the patient as all the interventions are done with the mother. Those mothers from the intervention arm randomly approached to participate in the follow-up interviews will be asked to consent to their interview being audio-taped and transcribed for ease of analysis. They will be assured that their thoughts and opinions will not be linked to them in any way during the analysis or presentation of results.

We do not feel that it is unethical to withhold the service of a lactation consultant for the control group as this is the current standard of care at CHEO. There is no study in the literature examining the impact of a breastfeeding support intervention on jaundiced infants admitted to hospital. Given the clear advantages that breastfeeding confers to the health of children, it is reasonable to conduct a clinical trial to determine the effectiveness of an intervention as we have described.

# 8. RELEVANCE OF STUDY AND DISSEMINATION FO RESULTS

The results of this study will clarify the importance of offering sound breastfeeding advice and accessible resources to mothers of young infants admitted to the hospital with jaundice, thus determining whether there truly is a need for trained lactation specialists in pediatric hospitals. It will further allow us to determine whether this particular population is truly at risk for early breastfeeding discontinuation. It will also allow us to determine whether a hospital-based breastfeeding support program can have a quantifiable impact on children’s health in their first 6 months of life, as measured by physician encounters and number and length of hospitalization. It will also help determine whether the implementation of a breastfeeding support program in the hospital will have an impact on the number of women seeking breastfeeding help post discharge. Lastly, it will allow us to collect information on the amount of support that is provided to breastfeeding women by their child’s primary care physician, potentially identifying a need for more rigorous breastfeeding training during residency.

The results of this study will be submitted for publication in peer-reviewed journals and submitted for presentation at appropriate scientific meetings. Results will also be provided to the heads of the academic health centres, to the hospitalist section of the Canadian Pediatric Society, and to the International Lactation Consultant Association (ILCA). They will pave the grounds for larger scale studies, with diverse infant populations.

**Appendix 1**

**Screening Log**

| **Screening #** | **Medical Record Number** | **Date of Visit**  **(dd/mm/year)** | **Eligible**  **for Study** | **Enrolled**  **in Study** | **If YES,**  **Enrollment**  **study #** | **If No, Why?**  **Circle**  **Reason** | **Signature** |
| --- | --- | --- | --- | --- | --- | --- | --- |
|  |  |  | **Y / N** | **Y / N** |  | 1-2-3 |  |
|  |  |  | **Y / N** | **Y / N** |  | 1-2-3 |  |
|  |  |  | **Y / N** | **Y / N** |  | 1-2-3 |  |
|  |  |  | **Y / N** | **Y / N** |  | 1-2-3 |  |
|  |  |  | **Y / N** | **Y / N** |  | 1-2-3 |  |
|  |  |  | **Y / N** | **Y / N** |  | 1-2-3 |  |
|  |  |  | **Y / N** | **Y / N** |  | 1-2-3 |  |
|  |  |  | **Y / N** | **Y / N** |  | 1-2-3 |  |
|  |  |  | **Y / N** | **Y / N** |  | 1-2-3 |  |
|  |  |  | **Y / N** | **Y / N** |  | 1-2-3 |  |
|  |  |  | **Y / N** | **Y / N** |  | 1-2-3 |  |

Legend : 1- Research Assistant not available

2- Family refused enrollment

3- Other

**Appendix 3**

**Lactation Consultant’s Intervention**

**Initial consultation**

Assessment of:

- Level of maternal physical discomfort
- Observation of positioning, latching, and sucking
- Signs of milk transfer
- Parental ability to identify infant feeding cues
- Mother-infant interaction and maternal response to feeding cues
- Maternal perception of infant satisfaction/satiety cues
- Woman’s ability to identify significant others who are available and supportive of breastfeeding
- Maternal breastfeeding self-efficacy

Education on:

- Benefits of breastfeeding
- Milk production
- Breastfeeding positions
- Latching/milk transfer
- Prevention and management of problems
- Recognizing feeding cues

Provide emotional support

Also, the lactation consultant will address the following:

- Teach proper use of breast pump
- Supply mother with pumping supplies
- Discuss safe milk storage practice
- Answer mother’s questions, address concerns
- Discuss follow-up plans

**Follow-up sessions:**

- Same as initial consultation
- Weigh baby
- Refer appropriately if concerns arise regarding baby’s health

**Appendix 4**

**Parent Diary**

**Patient Study Number: _________**

Please use this diary to record the types and amounts of food you have given your baby, the medical attention your baby has required, and the breastfeeding advice and help you have received.

This information should be recorded at the following times:

- one week after discharge from hospital
- when your baby is 2 months old
- when your baby is 4 months old
- when your baby is 6 months old

A research assistant will call you at these times to remind you to complete this diary. She will also ask you the same questions.

**REMEMBER**, please DO NOT disclose to this research assistant which study group you were assigned to (Lactation Consultant or Standard Care).

At the end of the study, please mail this diary back to:

Research Coordinator – Breastfeeding Study

[name]

Children's Hospital of Eastern Ontario

Department of Pediatrics

[name]

Ottawa, Ontario

[name]

If you have questions, please contact:

___________________, Research Coordinator, Breastfeeding Study

[contact] x______

[contact]

**Please complete 1 week post-hospital discharge:** ___________________ (date)

**Please record the types and quantities of food sources your child has been given or is currently receiving (please check and complete all sections that apply):**

□ *Breast Milk*

□ Currently, my child feeds at the breast an average of ____ times per 24 hour period. Each feeding lasts approximately ____ minutes.

□ Currently, my child receives expressed breast milk ____ times per 24 hour period. Each feeding is approximately ____ mL or ____ ounces.

□ My child is exclusively breast fed (receives only breast milk).

□ I completely stopped breastfeeding on _________________ (date)

□ *Formula*

□ I introduced my baby to formula on ________________ (date)

□ Currently, my child receives formula an average of ____ times per 24 hour period. Each feeding is approximately ____ mL or ____ ounces.

□ I stopped all formula on _________________ (date)

□ *Other milk (cow’s milk, soy milk, rice milk, goat’s milk, etc.)*

□ I introduced my baby to other milk on ________________ (date)

□ Currently, my child receives other milk an average of ____ times per 24 hour period. Each feeding is approximately ____ mL or ____ ounces.

□ I stopped all other milk on _________________ (date)

□ *Solids (pabulum, cereals, other prepared foods)*

□ I introduced my baby to solids on ________________ (date)

□ Currently, my child receives solids an average of ____ times per 24 hour period.

□ I stopped all solids on _________________ (date)

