**1.2 Study Objectives:**

*Primary Objectives*: To determine the effect of a breastfeeding support intervention on breastfeeding duration in breastfeeding infants admitted to the hospital with jaundice.

*Secondary Objectives:*

- To determine the rate of breastfeeding failure, defined as breastfeeding cessation before the infant turns 6 months, in mothers of jaundiced infants randomized to the control group, as compared to the rate of breastfeeding failure in the general population.
- To compare subsequent healthcare utilization between groups during their first six months of life, as determined by the number of re-hospitalizations for jaundice, hospitalizations for non-jaundice related causes, as well as physician encounters.
- To determine the number of mothers seeking breastfeeding help once discharged from the hospital and compare it between both groups.
- To determine the kind and perceived effectiveness of breastfeeding support and advice given by the infant’s primary physician throughout the child’s first six months of life.

*Hypothesis*: We hypothesize that, among mothers of breastfeeding infants who are admitted to hospital with jaundice, mothers who receive formal breastfeeding support will be more likely to exclusively breastfeed their infant at 3 months than mothers who receive the current standard of care.

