**4.7 Study Measurements:**

Baseline information about the infant and the infant’s mother will be recorded at the time of study enrollment. Information about the mother will include language spoken (French or English), maternal age, number of children prior to the participating infant, number of previously breastfed children, maternal education level, household income, marital status, maternal smoking history during pregnancy and after delivery, type of health care provider who followed the pregnancy, attendance at pre-natal classes. Information about the infant will include age, birth weight, gestational age at birth, weight on admission, weight on discharge, need for IV therapy during the hospitalization, septic work up done on admission, antibiotic treatment, length of stay, and the need for formula supplementation before admission, as well as during hospital stay (see Appendix 6).

Follow-up measurements will be collected until the infant is six months of age. Mothers will be given a booklet upon discharge from the hospital, where they will be asked to record the information on formula introduction, solid food introduction, timing of return to work, number of daily formula feeds and sessions at the breast at different points in time, number of hospitalizations and reason, number of visits to primary care physicians and reason, discussion with primary care physician regarding breastfeeding, number of visits to breastfeeding support (see Appendix 6).

A second research assistant, blinded to group allocation, will phone the participating mothers 1 week after discharge from the hospital to remind them to fill out their booklet, and to collect information regarding breastfeeding and formula feeding. Other phone calls will be placed again when the infant is 2, 3, 4 and 6 months old, to remind the mothers to fill out their booklets. The research assistant will also collect the same information the women are asked to record in their booklet, as a back up method in case the booklets are lost or not appropriately filled out. The research assistant will also remind the families, at the beginning of the phone call, not to disclose whether they were allocated to the control or to the study group so that the research assistant can remain blinded.

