**Other comments or information that you think might be relevant to the study:**

**Please complete when your child is 4 months of age:** __________________ (date)

**Please record the types and quantities of food sources your child has been given or is currently receiving (please check and complete all sections that apply):**

□ *Breast Milk*

□ Currently, my child feeds at the breast an average of ____ times per 24 hour period. Each feeding lasts approximately ____ minutes.

□ Currently, my child receives expressed breast milk ____ times per 24 hour period. Each feeding is approximately ____ mL or ____ ounces.

□ My child is exclusively breast fed (receives only breast milk).

□ I completely stopped breastfeeding on _________________ (date)

□ *Formula*

□ I introduced my baby to formula on ________________ (date)

□ Currently, my child receives formula an average of ____ times per 24 hour period. Each feeding is approximately ____ mL or ____ ounces.

□ I stopped all formula on _________________ (date)

□ *Other milk (cow’s milk, soy milk, rice milk, goat’s milk, etc.)*

□ I introduced my baby to other milk on ________________ (date)

□ Currently, my child receives other milk an average of ____ times per 24 hour period. Each feeding is approximately ____ mL or ____ ounces.

□ I stopped all other milk on _________________ (date)

□ *Solids (pabulum, cereals, other prepared foods)*

□ I introduced my baby to solids on ________________ (date)

□ Currently, my child receives solids an average of ____ times per 24 hour period.

□ I stopped all solids on _________________ (date)

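### The Parent Diary has no 3-month page or call time, so the 3-month phone call is the only same-time source for the primary outcome and contradicts the schedule mothers are given

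*Protocol*

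**What the plan says.** Section 4.8 of the Protocol sets the endpoint: "The primary outcome measured will be exclusive breastfeeding at 3 months, or 3 months corrected if the infant was born prematurely". Under its secondary outcomes the same section adds: "All measurements will be collected at corrected age if infant was born prematurely".

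Section 4.7 gives mothers a booklet at discharge. A second research assistant, blinded to allocation, phones one week after discharge, and then: "Other phone calls will be placed again when the infant is 2, 3, 4 and 6 months old". The stated purposes are to remind mothers to complete the booklet and to collect the same items by phone, as a back-up in case the booklet is lost or poorly completed. Section 6.1 repeats this call schedule.

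The booklet itself is Appendix 4. Its front page introduces a list with "This information should be recorded at the following times". The list is one week after discharge, "when your baby is 2 months old", then 4 months and 6 months. It continues: "A research assistant will call you at these times to remind you to complete this diary". The pages follow the same list. After the 2-month page the next one is headed "Please complete when your child is 4 months of age".

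**The concern.** The main record and the protocol body disagree about when data are collected, and they disagree at the primary time point. A mother reached at 3 months is reminded to complete a page that her booklet does not contain. The booklet has also told her to expect calls at other times.

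At stake is the quality of the one outcome on which the trial is powered. At 1 week, 2, 4 and 6 months there are two contemporaneous records, so one can stand in for the other or be checked against it. At 3 months there is only the call. If it is missed, 3-month status has to be worked out from later recall, and some mothers may end up missing or wrongly classified.

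The plain ages in the diary raise a second, smaller question. For a preterm infant they may not match the corrected age that section 4.8 requires.

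**Working it through.** **1. The schedules side by side**

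| Time | Calls, sections 4.7 and 6.1 | Times listed in Appendix 4 | Page in Appendix 4 |
| --- | --- | --- | --- |
| 1 week after discharge | yes | yes | yes |
| 2 months | yes | yes | yes |
| 3 months (primary outcome) | yes | no | no |
| 4 months | yes | yes | yes |
| 6 months | yes | yes | yes |

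The schedules differ at exactly one time, 3 months.

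**2. What remains if the 3-month call is missed**

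The 4-month page asks for the dates on which formula was introduced and stopped, other milk was introduced and stopped, and breastfeeding ended completely. The 4-month call asks the same questions. I read the outcome as feeding status at 3 months. For a mother who never used other milk, or who started it once and continued, these dates settle that status if she recalls them correctly.

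They may not settle it when formula use is interrupted. Each page has room for one formula start date and one stop date. Suppose formula is given in hospital, stopped, and restarted at some time between the 2-month and 4-month pages. If the mother enters the first introduction date, the restart date is recorded nowhere, and status at 3 months is unknown. This is not a remote case. Section 4.3 admits infants with any amount of breastfeeding, and the Appendix 6 form records formula given before and during admission. The feeding counts and the exclusivity tick box describe the present situation, so at 4 months they cannot simply be read back to 3 months.

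**3. Margin in the sample size**

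The stated size reproduces. With 50% against 75%, two-sided 0.05 and 80% power, the pooled mean is 0.625:

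n = [1.960 × √(2 × 0.625 × 0.375) + 0.842 × √(0.50 × 0.50 + 0.75 × 0.25)]² / 0.25² = 57.7, rounded up to 58 per group (power 80.2%).

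With 62 recruited and 7.5% lost, 62 × 0.925 = 57.35 remain, against 58 required. The allowance is 62 × 0.075 = 4.65 mothers per group, so there is no reserve beyond the planned loss. Nothing in this point changes the sample-size figures.

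**4. Corrected age**

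The eligibility criteria (section 4.3) set no gestational-age limit. As an illustration only, assume correction to 40 weeks:

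- Born at 36 weeks: 40 − 36 = 4 weeks. Three months corrected falls 4 weeks after 3 months plain age.
- Born at 35 weeks: 40 − 35 = 5 weeks.
- One month is 52 / 12 = 4.3 weeks. The 36-week infant therefore reaches 3 months corrected just before 4 months plain age, and the 35-week infant just after it.

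The protocol gives no share of preterm infants, so the number affected is unknown.

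**The case against.** The strongest reply is that the primary time point is covered. Sections 4.7 and 6.1 both specify a 3-month call by a blinded assistant who collects the booklet's items. Section 5.1 supports its low expected loss with earlier studies at the same hospital whose primary outcomes were obtained by phone, which suggests phone ascertainment was in mind. This stands. A reader might infer from Appendix 4 that the trial skips its own primary time point, and the protocol body does not support that.

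A reader might also infer that a single phone answer is the only information on the outcome. That goes too far. The 4-month page and call, and the 6-month page, ask for dates that bear on 3-month status. The call is the only contemporaneous source, not the only source.

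Third, a reader might conclude that calls to preterm infants fall at the wrong age. Section 4.7 does not say that its ages are chronological, and section 4.8 says all measurements are at corrected age. That sentence stands under the secondary outcomes but is worded generally. Read together, the two sections allow a call at corrected age. What remains is that the booklet in the mother's hands states plain ages with no instruction for preterm infants.

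None of this removes the contradiction in the call times or the missing page.

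**Conclusion.** The point holds as an inconsistency between a data-collection form and the protocol body, located at the primary time point. Appendix 4 omits 3 months both as a recording time and as a call time, while sections 4.7, 4.8 and 6.1 depend on it. In consequence, the primary outcome rests at its own time point on what section 4.7 describes as the back-up method, with a recall-based fallback that will usually, but not always, determine status.

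The missing page concerns the booklet of every planned participant (2 × 62 = 124). The number of outcomes actually lost or misclassified depends on the share of 3-month calls missed and on how often formula is stopped and restarted. The protocol gives neither, so I put no figure on it. The corrected-age mismatch is likewise of unknown size. The conclusion assumes that the booklet is issued as printed in Appendix 4. It should be corrected before booklets are handed out, because a same-time record that was not collected cannot be recovered in the analysis.

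**What to change.** - Add a 3-month page to Appendix 4, identical in content to the others, and add 3 months to the front-page list of recording and call times.
- State in section 4.7 that the 3-month call and the 3-month page are the source of the primary outcome, and that dates recorded later are the fallback when both are missing.
- For preterm infants, print corrected-age target dates in the booklet and use the same dates for the calls, so that sections 4.7, 4.8 and 6.1 and Appendix 4 agree.

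The cost is one extra diary page, a revised call calendar and a small added burden on mothers. The 3-month call is already planned, so no new visits or staff are needed.
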